### Data collection and management

Within the pragmatic trial, participating actors (physicians and exercise professionals) will assist with data collection for the effectiveness evaluation in the PARS group by handing out the questionnaires. For the PAA group, the questionnaire will be delivered by mail. The questionnaire comprises a compilation of reliable and validated survey instruments (see ‘Outcome measures’ above) and will be completed independently by the study participants. To ensure standardised data collection, the participating actors will prepare for this task in a special training session. Due to the personal supervision of the PARS group participants, the data will be collected by the same exercise professional at all three measurement time points. In the PARS group, participants will receive the questionnaires prior to the baseline and at the 12- and 24-weeks follow-up assessments, while PAA group participants will receive them by mail and are expected to return them to the study team with a prepaid envelope. The study team will periodically collect the documents of the PARS group from the participating medical and therapeutic practices. Adverse events will be assessed in both groups via questionnaires at both 12 and 24 weeks. In the case of a study dropout, the exercise professional in the PARS group can also report specific reasons.

The data for evaluating the implementation plan will be collected by the study team during and after the intervention period. For example, data on the characteristics of the participating actors (e.g. physicians and exercise professionals) will be collected during the intervention, while information about the success of the interventions will only be collected after their completion. Planned interviews or focus groups will be conducted by trained researchers from the FAU study team.

All data will be transcribed, pseudonymised, recorded, archived and evaluated by the research team using quantitative methods (descriptive and inferential statistics via, e.g. SPSS, R) and qualitative social research methods (e.g. transcription and coding of structured interviews via MAXQDA). The data will be stored securely, and only direct project members of the FAU will have access to them. The deletion of all collected data is planned after the legal retention period of 10 years, beginning with the end of the project duration (30.11.2022).

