After a 45-min initial assessment by the exercise professional, which is also part of the intervention, individually targeted PA promotion takes place over six sessions of 60 min each. The focus is on working out PA preferences with the patient, trying them and planning their subsequent implementation (e.g. in a regional exercise programme). For this purpose, exercise professionals can use a set of behavioural change techniques (BCTs), following Mitchie et al. [32], which has been identified as effective for PA behavioural change [33]. The BCTs are described in detail for both groups in Additional file 2. Exercise professionals in this study will focus particularly on the techniques of ‘goals and planning’, ‘feedback and monitoring’, ‘social support’, ‘shaping knowledge’ and ‘self-belief’. During the fourth session, a transfer to existing exercise or PA offers in the region will occur. Via a comprehensive brochure (more than 1000 offers from approximately 300 exercise providers), sorted by postal codes and types of offer, the participants will receive an overview of health-related PA opportunities and find the contact details for the respective exercise providers. After 12 weeks, a 45-min final assessment will take place to reflect on changes in the participant’s PA level and PAHCO and to formulate new goals for the next 12 weeks. The attending physician will receive feedback on the patient’s development. The transfer to existing PA programmes or independent activities will enable long-term maintenance of an active lifestyle, assessed in a follow-up assessment after a further 12 weeks. Before each assessment, participants will receive baseline or follow-up questionnaires to evaluate the effectiveness of the intervention and success of its implementation from their perspective. The questionnaires can be completed independently, although the treating exercise professional can assist with any questions.

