#### Physical activity advice (PAA)

After being screened for eligibility, the PAA group will receive similar brief PA advicePAA to the PARS group. However, instead of being referred to exercise professionals for a more intensive intervention, the PAA participants will then receive a brochure with PA information, steps to start PA and adopt a more active lifestyle, specific information about the diseases targeted in this study and concrete tasks. The brochure also contains materials on BCTs, in which the BCTs ‘goals and planning’, ‘feedback and monitoring’ and ‘shaping knowledge’ are used but to a lesser extent than in the PARS group. The major difference between the two groups is the social support from an exercise professional, which is not available in the PAA group. An overview of the integrated BCTs for the PAA group is included in Additional file 2.

Like the PARS group, the PAA group will also receive the overview of local PA offers. A baseline questionnaire and follow-up questionnaire to be completed after 12 and 24 weeks will be sent by mail with stamped envelopes for their return to the project team. If the questionnaire has not been answered after 14 days, participants will receive a reminder by mail. If participants in this intervention arm have any questions about the brochure or completing the questionnaires, they can contact the research team by phone or email in specific time slots.

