### Data analysis

A linear modelling approach will be used to analyse the effectiveness of the intervention. The group information (PARS vs PAA) will constitute the decisive independent variable to be modelled on participants’ outcomes after the intervention. In this context, participants’ baseline values will be integrated into the calculations to control for potential differences before the intervention. Given the clustered design, it is necessary to account for the nested character of the data (level 2: physicians; level 1: patients). Depending on the final number of clusters included (level 2), participants recruited (level 1) and the power achieved, either physicians will be included as a control variable or the hierarchical structure will be considered through multilevel structural equation modelling (applying the Kenward-Roger correction for small cluster sizes [45]).

Adopting an intention-to-treat paradigm, we will include all participants who have been randomised in the analysis. To avoid underestimation of treatment effects through conservative replacement strategies (such as baseline observation carried forward), we will apply imputation techniques to this trial. Accordingly, dropouts and missing data will be treated by applying full information maximum likelihood (FIML) imputation. The Mardia test, with its inspection of statistical skewness and kurtosis, will determine multivariate normality. If the assumptions of normality are violated, the calculations will be based on robust maximum likelihood (MLR) procedures.

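### Self-reported primary outcomes pass through the treating exercise professional in PARS but by post to the study team in PAA, so collection procedure coincides with arm

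*Protocol article*

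**What the plan says.** The primary hypotheses concern subjective physical activity and PAHCO at 12 and 24 weeks. Both are measured by questionnaire (Protocol article, Primary hypotheses and Primary outcomes).

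**PARS.** Data collection and management states that "In the PARS group, participants will receive the questionnaires prior to the baseline and at the 12- and 24-weeks follow-up assessments" and that "the data will be collected by the same exercise professional at all three measurement time points". On completion of the forms, the section on the PARS intervention says: "The questionnaires can be completed independently, although the treating exercise professional can assist with any questions". The first of these visits is itself treatment: "After a 45-min initial assessment by the exercise professional, which is also part of the intervention". On return of the forms: "The study team will periodically collect the documents of the PARS group from the participating medical and therapeutic practices".

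**PAA.** The questionnaires go out by mail at baseline, 12 and 24 weeks and come back to the project team in a prepaid envelope. "If the questionnaire has not been answered after 14 days, participants will receive a reminder by mail". Questions go to the research team by phone or email (Physical activity advice, and Data collection and management).

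**Blinding and analysis.** Exercise professionals cannot be blinded (Randomisation, allocation and blinding). The Data analysis section adjusts for baseline values, says "we will include all participants who have been randomised in the analysis", and treats dropouts and missing data by full information maximum likelihood (FIML).

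**The concern.** The collector, the person who may help, the route of return and the handling of non-response all differ by arm, and they differ completely. No analysis can separate an effect of treatment from an effect of the collection procedure when the two coincide.

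Two mechanisms matter. The first is reporting. A PARS participant describes activity and competence in a form that goes to their own coach. The 12-week form surrounds a meeting held to review change in those same two constructs. A PAA participant writes to researchers. Any tendency to please the coach would enter the PARS mean only.

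The second is missing data. In PARS the forms follow the visits, so a participant who does not take up the referral or stops attending may be harder to reach, and no attendance-independent route or reminder is described for that arm. In PAA a participant who does nothing with the brochure is still mailed and reminded. Missingness in PARS can therefore follow adherence.

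At stake is whether a significant difference on any of the four primary tests can be read as an effect of the referral scheme.

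**Working it through.** **1. The plan's own figure.** Inputs from the Sample size section: f = 0.175 (d = 2 × 0.175 = 0.35 for two equal groups), α = 0.05/4 = 0.0125 per test (taken as two-sided), power 80%, ICC 0.02, dropout 10%, 24 practices, 567 participants.

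- Unclustered total: 4 × ((2.498 + 0.842)/0.35)² ≈ 364.1.
- Evaluable participants per practice: 567 × 0.9/24 = 21.26.
- Design effect: 1 + (21.26 − 1) × 0.02 = 1.405.
- Total with clustering and dropout: 364.1 × 1.405/0.9 ≈ 569.

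The stated 567 is reproduced to within rounding (power at 567 is 0.799). Nothing in this point disputes it.

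**2. Precision of the comparison.** Evaluable n = 567 × 0.9 = 510.3. Effective n = 510.3/1.405 = 363.1, about 181.6 per arm. Standard error of the difference = √(4/363.1) = 0.105 SD.

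**3. Reporting shift with no true effect.** Let s be the net shift in favour of PARS that remains after baseline adjustment. The documents give no value for s, so the range is an assumption. The chance of a significant result per test is P(Z > 2.498 − s/0.105) + P(Z < −2.498 − s/0.105), by normal approximation.

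| s (SD) | s as a share of d = 0.35 | Chance of significance |
|---|---|---|
| 0 | 0% | 0.0125 |
| 0.05 | 14% | 0.023 |
| 0.10 | 29% | 0.062 |
| 0.15 | 43% | 0.143 |
| 0.20 | 57% | 0.277 |

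**4. Selective missing data in PARS.** Suppose a proportion p of PARS participants is unobserved and their mean lies g SD below that of observed participants, beyond what FIML can explain from the modelled variables. The bias in the PARS mean is about p × g. Both inputs are assumptions, except that 10% is the protocol's single dropout rate.

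- p = 10%, g = 0.5: 0.05 SD
- p = 20%, g = 0.5: 0.10 SD
- p = 30%, g = 0.5: 0.15 SD

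Selective non-response in PAA would offset this bias in whole or in part.

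**The case against.** There are real safeguards. Data collection and management says that participants complete the questionnaires independently and that the actors are trained to standardise collection. Help is available in both arms. Baseline values are in the model and, because the route differs at baseline too, adjustment can remove part of a constant mode effect. These points stand, and they make this a risk of bias rather than a demonstrated bias. They do not dispose of it. Training standardises procedure within PARS and does not make the arms alike. The helper in PARS is the treating professional. The baseline form precedes the coaching, so adjustment cannot remove desirability that develops over the six sessions.

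A reader might also infer four stronger things that the documents do not support:

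- **That PAA reporting is anonymous.** Data are pseudonymised, and a reminder to non-responders means that returns are tracked. The contrast is treating provider versus study team.
- **That PARS participants who stop attending yield no follow-up data.** The article does not say so. Physicians also help to hand out questionnaires, and documents are collected from medical as well as therapeutic practices. A condensed article may leave follow-up of non-attenders to the full protocol.
- **That the intention-to-treat statement is false.** Inclusion of all randomised participants with FIML is a coherent plan under missing at random. Adherence-linked dropout makes that assumption harder to defend; it does not contradict the statement.
- **That the bias must favour PARS.** Unmotivated PAA participants may also fail to return a postal form, which would raise the observed PAA mean and push the other way.

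**Conclusion.** The concern holds as a stated design weakness, not as a gap in the article: the protocol describes two different collection procedures for self-reported primary outcomes, aligned with arm, one of them run by the unblinded treatment provider. The comparison is exposed to differential reporting and, less certainly, to adherence-linked missing data in PARS. FIML deals with the latter only if the data are missing at random given the modelled variables.

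The size is unknown. If the net shift were 0.10 SD, the error rate per test would be about five times nominal (0.062/0.0125); at 0.20 SD about 22 times (0.277/0.0125). These figures rest on assumed shifts, a two-sided test, the planned ICC and dropout, and a normal approximation. The direction is likely, but not certain, to favour PARS. Uniform collection is a cheap improvement that should be made; the present procedure does not by itself show the result to be wrong.

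**What to change.** Use the PAA procedure in both arms.

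- The study team mails the 12- and 24-week questionnaires, and the baseline form where still possible, to every consented participant on dates counted from enrolment. This includes PARS participants who never attended or who stopped.
- Forms return prepaid to the study team, with the same 14-day reminder, and questions go to the research team.
- Exercise professionals neither handle nor assist with outcome questionnaires. They may keep their own assessment for goal setting.
- Baseline needs the same treatment. If it stays with the exercise professional while follow-up moves to post, PARS acquires a change of mode within the arm that PAA lacks, and baseline adjustment is weakened.
- The Trial status section lists the trial as recruiting. Record the collection mode of every form already obtained and report a sensitivity analysis by mode. Mode will not have been randomised within PARS, so that analysis is supportive only.

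The cost is an amendment and postage for the PARS arm, about 284 participants if the arms are equal (567/2). The mailing process already exists, so no extra staff should be needed, and the sample size does not change. The downside is that PARS returns may come later, or be somewhat fewer, than with handover in person.

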### Data analysis

A linear modelling approach will be used to analyse the effectiveness of the intervention. The group information (PARS vs PAA) will constitute the decisive independent variable to be modelled on participants’ outcomes after the intervention. In this context, participants’ baseline values will be integrated into the calculations to control for potential differences before the intervention. Given the clustered design, it is necessary to account for the nested character of the data (level 2: physicians; level 1: patients). Depending on the final number of clusters included (level 2), participants recruited (level 1) and the power achieved, either physicians will be included as a control variable or the hierarchical structure will be considered through multilevel structural equation modelling (applying the Kenward-Roger correction for small cluster sizes [45]).

Adopting an intention-to-treat paradigm, we will include all participants who have been randomised in the analysis. To avoid underestimation of treatment effects through conservative replacement strategies (such as baseline observation carried forward), we will apply imputation techniques to this trial. Accordingly, dropouts and missing data will be treated by applying full information maximum likelihood (FIML) imputation. The Mardia test, with its inspection of statistical skewness and kurtosis, will determine multivariate normality. If the assumptions of normality are violated, the calculations will be based on robust maximum likelihood (MLR) procedures.

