### Sample size

To calculate the number of participants, we focus on the primary endpoints of ‘moderate to vigorous PA (min/week)’ and ‘PAHCO’, including cluster adjustment. As the primary outcomes lead to four statistical tests, a Bonferroni correction is used accordingly with *α *= 0.05/4. With an assumed drop-out rate of 10%, a sample size of 567 participants from 24 medical practices (α = 0.0125, power = 80%) is required to detect differences between both intervention groups of low to moderate effect size (*f* = 0.175). To account for the effects of clustering, an intraclass correlation (ICC) of 0.02 is considered, estimated based on previous studies for cRCTs in primary care [26, 27]. We consider this ICC to be realistic in our trial as the participating practices are similarly structured (professional background, qualification level, treating patient group size and region) and were trained by the research team.

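### The Kenward-Roger correction is attached to a multilevel SEM estimated by FIML or MLR, for which it is not defined, so the multilevel branch of the analysis cannot be run as specified

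*Protocol article*

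**What the plan says.** The Data analysis section of the protocol article announces linear modelling with group as the key predictor and adjustment for baseline. For the nesting of patients it leaves two routes open, to be chosen later from the clusters and participants obtained and the power achieved. One enters physicians as a control variable. The other is multilevel structural equation modelling, "applying the Kenward-Roger correction for small cluster sizes".

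The next paragraph fixes the estimator: "dropouts and missing data will be treated by applying full information maximum likelihood (FIML) imputation". If normality is rejected, "the calculations will be based on robust maximum likelihood (MLR) procedures". No REML mixed model is named.

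The Sample size section sets the error rate these tests must hold: "As the primary outcomes lead to four statistical tests, a Bonferroni correction is used accordingly", which gives 0.05/4 = 0.0125 per test. It also sets the number of randomised units: "With an assumed drop-out rate of 10%, a sample size of 567 participants from 24 medical practices".

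**The concern.** The section names a model, an estimator, a small-sample correction and a fallback, and they do not fit together. Kenward-Roger adjusts the covariance matrix of the fixed effects from a REML fit and supplies denominator degrees of freedom. FIML is full maximum likelihood, normally tested with Wald z statistics. MLR replaces the model-based variance with a sandwich and still refers the result to z. The correction is defined for neither.

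The wording also misplaces the problem. Clusters of about 21 are not especially small. What calls for a correction is that only 24 practices are randomised, which leaves about 22 degrees of freedom for the arm comparison.

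At stake is the per-test level of 0.0125 that the Bonferroni division is meant to secure. In the far tail, a z reference and a variance biased downwards cost proportionally more than at 0.05.

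**Working it through.** **Inputs from the Sample size section.** α = 0.0125 per test, power 80%, f = 0.175 (d = 2f = 0.35 for two groups), ICC 0.02, 24 practices, 10% dropout, N = 567. **Assumptions:** two-sided tests, 12 practices per arm, equal cluster sizes, no baseline covariate.

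**1. The protocol's own figure.** n per arm = 2(2.498 + 0.842)²/0.35² = 182.1, so 183, or 366 in total. Completers per practice: m = 0.9 × 567/24 = 21.26. Design effect: 1 + 20.26 × 0.02 = 1.405. Completers needed: 366 × 1.405 = 514. Dividing by 0.9 gives 572 (multiplying by 1.1 gives 566). So 567 is reproduced to within 1%, by a calculation that makes no allowance for few clusters.

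**2. Cluster sandwich with z (the MLR-type test).** In a balanced design the uncorrected sandwich variance equals the unbiased between-practice variance times 22/24. True size = P(|t₂₂| > 2.498 × √(22/24)) = P(|t₂₂| > 2.391) = 0.0258, or 2.1 times nominal.

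**3. ML with z.** This depends on the ICC, because the between-practice variance is truncated at zero. Simulation of a balanced random-intercept model, 24 practices of 21, nominal 0.0125 (1,000,000 runs per row):

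| ICC | ML, z | Sandwich, z |
|---|---|---|
| 0 | 0.011 | 0.026 |
| 0.01 | 0.016 | 0.026 |
| 0.02 | 0.020 | 0.026 |
| 0.05 | 0.025 | 0.026 |
| 0.10 | 0.026 | 0.026 |

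A separate simulation at ICC 0.02 gave 0.0208 for ML, hence 2.0–2.1%, or 1.6–1.7 times nominal. At the same ICC, REML with 22 df gives 0.010, and REML with Kenward-Roger-like df gives 0.012. Both control the level.

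**4. Other numbers of practices, ICC 0.02.**

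| Practices × patients | ML, z | Sandwich, z |
|---|---|---|
| 36 × 14 | 0.017 | 0.021 |
| 24 × 21 | 0.020 | 0.026 |
| 16 × 21 | 0.022 | 0.035 |
| 12 × 21 | 0.024 | 0.046 |

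The 36 row is shown because the block sizes in the Randomisation section add up to 10 + 2 + 10 + 2 + 10 + 2 = 36.

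**5. Four primary tests.** Bonferroni bound: 4 × 0.0208 = 0.083 (ML) and 4 × 0.0258 = 0.103 (sandwich on all four). If independent: 1 − (1 − 0.0208)⁴ = 0.081 and 1 − (1 − 0.0258)⁴ = 0.099. With assumed equal correlation of 0.3, 0.5 or 0.7 among the four statistics, the sandwich case falls to 9.7%, 8.4% or 7.2%.

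**6. Power under a t reference.** Effective N = 510.3/1.405 = 363. Noncentrality = 0.35 × √363/2 = 3.33. With z (critical value 2.498) power is 0.80. With t on 22 df (critical value 2.720) it is 0.73.

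**The case against.** A reader might infer that the small-cluster protection will simply be lost and that type I error therefore doubles. The document does not support that. It states that the correction will be applied. With an observed outcome and one group contrast, a two-level SEM reduces to a random-intercept mixed model, which can be refitted by REML with Kenward-Roger. An analyst who resolves the conflict that way keeps the error rate under control. The source cited for this step is not at hand and might show that this was intended. This objection stands: losing the correction is one possible outcome, not a stated one.

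Doubling is not the base case either. It needs MLR, or an ICC of about 0.05 or more. MLR is conditional on the normality check. Skewed activity minutes make it plausible for that outcome, but the protocol gives no distribution, and nothing suggests it for the bounded competence scores. The 10% family-wise figure needs MLR on all four tests. Measurements on the same patients are likely to be positively correlated, which lowers the figure further.

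Finally, only one of two routes is affected. The other is no refuge: it carries no small-sample correction, and arm is constant within a practice, so practice-level fixed effects would be collinear with it. That is a separate matter.

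None of this removes the mismatch. The text names no REML model, and its FIML and MLR rules point away from one.

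**Conclusion.** The concern holds as a specification error in the multilevel route: the named correction is not defined for the named estimators, so the analysis cannot be carried out as written. The phrase about cluster sizes should refer to the number of clusters.

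The consequence is conditional. If the SEM with FIML or MLR is kept and the correction dropped, per-test error at nominal 1.25% is about 2.0–2.1% under ML at ICC 0.02 and about 2.6% under an MLR-type sandwich. Under ML there is no inflation at ICC 0, and 2.5% is reached at ICC 0.05. Family-wise error is then at most about 8% (ML) to 10% (MLR throughout). If Kenward-Roger is kept and the SEM dropped, there is no inflation. Confidence is high in the mismatch and lower in the size of its effect, which rests on balanced clusters, 24 practices and two-sided tests. It should be corrected before analysis.

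**What to change.** Choose one of two wordings for the multilevel route:

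- Name as primary analysis a linear mixed model fitted by REML, with a random practice intercept, baseline adjustment and Kenward-Roger degrees of freedom, using all available follow-up under missing at random.
- Or keep the multilevel SEM, delete the Kenward-Roger wording and specify a small-sample method that is valid for it with few clusters.

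In either case, refer to a small number of clusters. For non-normal outcomes, replace plain MLR with a few-cluster method such as a CR2 variance with Satterthwaite degrees of freedom.

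The cost is analysis wording, with no new data. Under the first option the SEM framework is given up and patients with a missing baseline need stated handling. A t reference with about 22 df also lowers power from about 0.80 to about 0.73 on the protocol's own assumptions, without counting any gain from baseline adjustment. The sponsor should know this when fixing the analysis.
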